## Abstract

**Introduction:**

Self-monitoring of blood pressure (BP) in pregnancy could improve the detection and management of pregnancy hypertension, while also empowering and engaging women in their own care. Two linked trials aim to evaluate whether BP self-monitoring in pregnancy improves the detection of raised BP during higher risk pregnancies (BUMP 1) and whether self-monitoring reduces systolic BP during hypertensive pregnancy (BUMP 2).

**Methods and analyses:**

Both are multicentre, non-masked, parallel group, randomised controlled trials. Participants will be randomised to self-monitoring with telemonitoring or usual care. BUMP 1 will recruit a minimum of 2262 pregnant women at higher risk of pregnancy hypertension and BUMP 2 will recruit a minimum of 512 pregnant women with either gestational or chronic hypertension. The BUMP 1 primary outcome is the time to the first recording of raised BP by a healthcare professional. The BUMP 2 primary outcome is mean systolic BP between baseline and delivery recorded by healthcare professionals. Other outcomes will include maternal and perinatal outcomes, quality of life and adverse events. An economic evaluation of BP self-monitoring in addition to usual care compared with usual care alone will be assessed across both study populations within trial and with modelling to estimate long-term cost-effectiveness. A linked process evaluation will combine quantitative and qualitative data to examine how BP self-monitoring in pregnancy is implemented and accepted in both daily life and routine clinical practice.

**Ethics and dissemination:**

The trials have been approved by a Research Ethics Committee (17/WM/0241) and relevant research authorities. They will be published in peer-reviewed journals and presented at national and international conferences. If shown to be effective, BP self-monitoring would be applicable to a large population of pregnant women.

**Trial registration number:**

NCT03334149

Strengths and limitations of this studyBased on current literature, these will be the largest randomised controlled trials of blood pressure self-monitoring in pregnancy completed to date.The pragmatic trial designs, with broad inclusion criteria, will make findings of both linked studies applicable to routine antenatal care.Data on the correct targets for self-monitored blood pressure are currently sparse.The trials are powered for primary and some secondary outcomes but the effect of self-monitoring on rarer secondary maternal morbidity and mortality outcomes will still be uncertain.Women with gestational hypertension may develop this late in pregnancy making it harder to show benefit for interventions at this time.

## Introduction

Raised blood pressure (BP) affects approximately 10% of pregnancies worldwide, almost half of these women develop pre-eclampsia.^1^ Globally, around 15% of maternal mortality is due to pre-eclampsia so early detection and prevention are paramount.^2^ In the UK, inadequate management of raised BP, in particular systolic hypertension, has previously been reported as a significant contributing factor to maternal deaths and although this has improved over the past decade, pre-eclampsia remains important.^3 4^

BP self-monitoring, where an individual measures their own BP outside of the clinical setting, allows for multiple measurements providing a better estimate of the underlying BP than intermittent clinic measurements. Such self-monitoring in pregnancy could improve both the detection and subsequent management of gestational hypertensive disorders including pre-eclampsia, while also empowering and engaging women in their own care.^5 6^

Women who are at higher risk for raised BP in pregnancy (eg, due to age or previous medical history) may require more frequent monitoring.^7 8^ BP can rise rapidly in pregnancy and hypertension may go undetected in between antenatal visits.^2^ Once raised BP is detected during the pregnancy, the clinical focus is on treating the hypertension, monitoring for development of pre-eclampsia and ensuring appropriate fetal surveillance.^7^ Substantial resources are currently expended in monitoring such women, from the perspective of both the woman and the National Health Service (NHS).^9^ If shown to be successful, self-monitoring could provide more accurate data for clinicians to use for treatment and management strategies, safely reduce the burden of multiple clinic visits for women, free up time for midwives and therefore be a cost-effective option. Self-monitoring is easy to accomplish and is now commonplace in adults with hypertension outside of pregnancy.^10 11^

BP self-monitoring is, therefore, a potentially appealing option for both the detection and management of hypertension. We have previously shown feasibility and acceptability of self-monitoring of BP in pregnancy.^5 6^ This trial aims to investigate self-monitoring in two groups by undertaking two linked, parallel group, randomised trials to evaluate whether self-monitoring of BP improves the detection of raised BP during higher risk pregnancies (BUMP 1) and whether self-monitoring improves BP control in women with hypertensive pregnancy (BUMP 2).

## Methods and analysis

### Study design and setting

The BUMP trials are two linked, multicentre, non-masked, parallel group, randomised controlled trials investigating self-monitoring of BP during pregnancy in the UK in secondary care maternity units (sites listed on https://clinicaltrials.gov/ct2/show/NCT03334149). The work is part of a larger programme of work investigating the use of self-monitoring and testing during pregnancy.

The BUMP 1 trial is a prospective non-masked randomised controlled trial of self-monitoring of BP in pregnancy for the detection of raised BP. Women at higher risk of pre-eclampsia will be recruited through antenatal clinics. The consent process for BUMP 1 will include discussion of the transition to BUMP 2 should a woman develop raised BP.

The BUMP 2 trial is a prospective non-masked randomised controlled trial of self-monitoring of BP for the management of hypertension in pregnancy in women with chronic hypertension (CH) or gestational hypertension (GH). Women may enter this study from BUMP 1 (maintaining original randomisation) or be recruited without prior involvement. See figure 1 for an overview of the study design.

**Figure 1 F1:**
[figure not shown]
Study design. BUMP 1, BP during higher risk pregnancy; CH, chronic hypertension; GH, gestational hypertension; HT, hypertension; NT, normotension.

There will be an initial external pilot phase including up to 50 women in order to test trial procedures prior to the commencement of full recruitment.

### Intervention and controls groups

#### Usual care

Usual care will consist of pregnant women having their BP measured by their usual antenatal care team, and initiation and/or adjustment of medication (where appropriate) based on these measurements at the discretion of the healthcare professional.

#### Self-monitoring

Women randomised to self-monitoring will be provided with a monitor validated for use in pregnancy and pre-eclampsia (Microlife WatchBP Home) and instructions for its use. Participants will be enrolled on the telemonitoring system, a text/app-based system and provided with clear instructions on its use. Participants can switch between the text and app system to decrease problems with connectivity for example, poor internet connection or phone signal. Access to the telemonitoring system was designed to have secure logins for the participants, their clinicians and the research team. This system was developed from our pilot work with appropriate theoretical underpinnings and designed by the University of Oxford, Department of Engineering Science, and appropriate functionality testing was done by the development team to test different combinations of normal and abnormal BP readings and user behaviours (eg, poor adherence or numerous, unrequested readings) over a prolonged period followed by user testing with pregnant women.^6 12^

BUMP 1 participants will be asked to monitor their BP three times a week throughout their pregnancy. They will be instructed to sit quietly and comfortably for 1 min, take two readings 1 min apart and submit their second reading to the telemonitoring system. Participants will receive a guideline with colour-coded instructions (figure 2). If the second reading is outside the expected range, this will automatically trigger a request for a third reading (taken after 5 min) and persistent high or low readings will automatically trigger a message to ask the participant to contact their local maternity unit. If women have persistently high readings, they will be asked (via the telemonitoring system) to undertake daily readings for the rest of their pregnancy.

**Figure 2 F2:**
[figure not shown]
BP interpretation chart for BUMP 1. BUMP1, BP during higher risk pregnancy.

BUMP 2 participants will be asked to monitor their BP daily throughout their pregnancy. They will be instructed to take two measures (as above) and asked to submit their second reading to the telemonitoring system. Participants will receive a guideline with colour coded instructions (figure 3). High or low second readings will automatically trigger a request for a third reading (taken after 5 min) and persistent high or low readings will automatically trigger a message for the participant to contact their local maternity unit.

**Figure 3 F3:**
[figure not shown]
BP interpretation chart for BUMP 2. BUMP 2, BP during hypertensive pregnancy.

On the basis of the results of our pilot work and recent systematic review, the same thresholds will be used for self-monitoring as clinic BP to trigger action (ie, 140/90 mm Hg), therefore, resulting in alerts to participating women via the telemonitoring system.^6 13^

To improve adherence to the intervention participants will receive weekly motivational messages, and these messages will be sent to women in the intervention group via the telemonitoring system (via the app or text message) based on the woman’s preference. These are designed to provide support and education throughout the trial and were developed during our pilot work with patient and public involvement. Messages will be selected at random from a pool of messages (approved by the ethics committee). To monitor adherence and for safety the local clinical team will also receive warnings in real time via the telemonitoring system if a participant misses submitting readings, allowing them to approach the participant to troubleshoot any potential issues.

Participants will be provided with instructions in the use of the telemonitoring system at the baseline visit. Participants will manually send their readings from the BP monitor to a centralised database, secured behind NHS firewalls, using a free SMS text message or app with web-based data entry backup. Reminders and triggered messages will be received by participants according to a rule-based algorithm developed with the clinical team. Participants in BUMP 1 will receive a reminder after 4 days without submitting a reading and then one more reminder the following day if no further readings are entered. Participants in BUMP 2 will receive a reminder after two missed days of readings, with a further reminder the following day if no further readings are entered.

Each participant has the right to discontinue the intervention or withdraw from the trial at any time. In addition, an investigator may withdraw a participant from the trial at any time if the investigator considers it necessary for any reason including: ineligibility (either arising during the trial or retrospectively having been overlooked at screening), an adverse event (AE), which results in inability to continue to comply with trial procedures, withdrawal of consent and lost to follow-up. If a woman discontinues the intervention, withdraws or is withdrawn from the study at any point, her usual antenatal care will continue as all study procedures are additional rather than in place of usual care.

Women who wish to discontinue the BP self-monitoring intervention will be asked if they are willing to participate in study follow-up. All data collected to the point of withdrawal will be retained in the study database. Unless a participant specifically withdraws consent, notes review will be conducted if possible, even where an individual has been lost to follow-up.

### Study outcomes

#### Outcome definitions

The onset of hypertension/high BP will be defined as the earliest date recorded of sustained systolic BP ≥140 and/or diastolic BP ≥90 mm Hg from any community or hospital setting recorded in the notes review.Sustained is defined as at least two readings within 1 week (168 hours), with no minimum time between readings needing to be recorded.The ‘earliest date recorded’ will be for the second of these two readings.Additionally, a new prescription of antihypertensive medication for raised BP will be taken as a diagnosis of hypertension/high BP (in order to capture diagnoses where medication has been started but two raised BPs have not been recorded in the notes review for whatever reason). In this case, the first date of prescription will be listed as the date of diagnosis.

#### Primary outcome for BUMP 1

The primary outcome for BUMP 1 is the difference in time to a recording of raised BP by a healthcare professional between the usual care and self-monitoring groups.

#### Secondary outcomes for BUMP 1

Secondary outcomes for BUMP 1 include analysis of the difference between usual care and self-monitoring groups as per box 1:

Box 1Secondary outcomes for blood pressure (BP) during higher risk pregnancy (BUMP 1) and BUMP 2Maternal outcomesSevere hypertension (systolic BP ≥160 mm Hg and/or diastolic BP ≥110 mm Hg).Pre-eclampsia or gestational hypertension.Serious maternal complications including eclampsia, transient ischaemic attack or stroke, pulmonary oedema, renal failure, blood transfusion, HELLP syndrome, liver involvement, haematological involvement and death.Onset of labour.Change in maternal quality of life from randomisation (measured using the EuroQoL 5 Dimensions 5 Levels (EQ-5D-5L) questionnaire).^16^Diastolic BP.*****Area under the BP curve.*****Proportion of systolic readings above 140 mm Hg.*****Perinatal OutcomesStillbirths.Early neonatal deaths.Gestation at delivery.Mode of delivery.Birth weight of the baby, including centile.Small for gestational age infants (<10th and <3rd centile).Neonatal unit admissions, including length of stay.Process outcomesChange in health behaviours (questionnaire).Fidelity to monitoring schedule.Change in State Trait Anxiety Inventory short form 6 anxiety questionnaire.^34^Health service costs.Cost per maternal quality-adjusted life year gained over trial period.Change in adherence to medication (MARS questionnaire).***^35^**Qualitative data gathered from participating women and healthcare professionals.Outcomes common to both trials apart from. *Only assessed on BUMP 2 participants.

#### Primary outcome for BUMP 2

The primary outcome for BUMP 2 is the difference in mean systolic BPs, recorded by healthcare professionals from baseline to delivery, between usual care and self-monitoring groups.

#### Secondary Outcomes for BUMP 2

Secondary outcomes for BUMP 2 include analysis of the difference between usual care and self-monitoring groups as per box 1.

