Box 2Blood pressure during higher risk pregnancy (BUMP 1) inclusion and exclusion criteriaInclusion criteriaParticipant is willing and able to give informed consent for participation in the trial.Pregnant woman, aged 18 years or above between 16+^0^ and 24+^0^ weeks.Able and willing to comply with trial requirements.Willing to allow her general practitioner and consultant, if appropriate, to be notified of participation in the trial.At higher risk for hypertension in pregnancy/pre-eclampsia defined as one or more of the following risk factors:Age 40 years or older.Nulliparity.Pregnancy interval of more than 10 years.Family history of pre-eclampsia.Previous history of pre-eclampsia or gestational hypertension.Body mass index 30 kg/m^2^ or above at booking.Chronic kidney disease.Twin pregnancy.Prepregnancy diabetes (type 1 or 2)Autoimmune disease (eg, systemic lupus erythematosus or antiphospholipid disease).Exclusion criteriaChronic hypertension.

Box 3Blood pressure (BP) during hypertensive pregnancy inclusion and exclusion criteriaInclusion criteriaWomen with chronic hypertension (defined as sustained systolic BP ≥140 mm Hg and/or diastolic BP ≥90 mm Hg, present at booking or before 20 weeks gestation, or receiving antihypertensive treatment outside pregnancy and/or at time of referral), recruited up to 37+^0^ weeks gestation.ORWomen with gestational hypertension after 20 weeks gestation (defined as sustained systolic BP ≥140 mm Hg and/or diastolic BP ≥90 mm Hg), recruited at 20+^0^ to 37+^0^ weeks gestation.ANDParticipant is willing and able to give informed consent for participation in the trial.Woman aged 18 years or above.Willing to allow her general practitioner and consultant, if appropriate, to be notified of participation.Exclusion criteriaAnticipated inpatient admission considered likely to lead to imminent delivery (within the next 48 hours).

**Table 1 T1:** Schedule of interventions and assessments

	Study period (16 weeks to 8 weeks postdelivery)			
Study visit	Trial entry/baseline	Antenatal follow-up	Notes review	Postnatal follow-up
Time point	20±4 weeks gestation	30±3 weeks gestation	40+4 weeks (postdelivery)	40+8 weeks (postdelivery)
Informed consent	X			
Eligibility assessment	X			
Demographics; including age, race, education	X			
Maternal demographics; including gestation, EDD and parity	X			
Patient Questionnaires; including EQ-5D-5L and STAI	X	X		X
Randomisation	X			

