#### BP during hypertensive pregnancy

An ITT analysis will include women recruited to BUMP 1 who become hypertensive and women recruited de novo to BUMP 2 with GH and CH analysed separately. The primary analysis for BUMP 2 will in each case compare BPs between the intervention and control groups. Analysis of the BP outcome will be by means of a linear mixed-effects model, which can accommodate data where participants have repeated measurements, and also accounts for missing data (assuming data are missing at random). Each of a participant’s BP measures will be modelled by means of a linear mixed-effects model, including random effects for participants and assuming an unstructured variance covariance matrix between measurements from the same participant. Time of BP measurement and randomised group, as well as their interaction term, will be included as fixed effects in the model. A fixed effect will also be included for whether the participant was from BUMP 1 or not in the GH analysis. As a sensitivity analysis inclusion from BUMP 1 or not will be tested as a moderator of the treatment effect. By means of appropriate contrasts, the difference in mean BP of participants in the randomised groups from both BUMP 1 and de novo recruitment will be compared.

BP load and area under the curve will be analysed as continuous outcomes by means of a linear regression model, adjusting for whether the participant originated from BUMP 1. Continuous secondary outcomes, such as birth weight and length of stay, will be analysed by means of regression model. Binary secondary outcomes, such as the development of severe hypertension, incidence of complications and incidence of stillbirth, will be analysed by means of a log binominal model.

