#### Subgroup analyses

For both BUMP 1 and BUMP 2 prespecified subgroups include eligibility for aspirin prescription to prevent pre-eclampsia (as per National Institute for Health and Care Excellence); gestational age at baseline (≤20 weeks vs >20 weeks), parity (0 vs ≥1). In addition, a sensitivity analysis will compare those women with GH that are recruited de novo into BUMP 2 with those that migrate from BUMP 1.

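### In BUMP 2 every woman with gestational hypertension already meets the secondary outcome of pre-eclampsia or gestational hypertension at entry, so it gives no pre-eclampsia estimate in that stratum

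*Protocol article*

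**What the plan says.** Box 1 (Study outcomes) is a single list serving both trials. It includes "Pre-eclampsia or gestational hypertension" without an asterisk. The footnote reads "Outcomes common to both trials apart from. *Only assessed on BUMP 2 participants", so an item without an asterisk belongs to BUMP 2 as well as BUMP 1. Pre-eclampsia does not appear as an item of its own.

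Box 3 admits two kinds of women to BUMP 2. Women with CH are "recruited up to 37+^0^ weeks gestation", with no lower limit. Women with GH arising after 20 weeks are "recruited at 20+^0^ to 37+^0^ weeks gestation". Women from BUMP 1, enrolled "between 16+^0^ and 24+^0^ weeks", pass into BUMP 2 if they become hypertensive and keep their original allocation (Sample size considerations; Randomisation).

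The BUMP 2 analysis section states that GH and CH are analysed separately and that binary secondary outcomes are fitted with a log binomial model. The Subgroup analyses section sets one cut for both trials: "gestational age at baseline (≤20 weeks vs >20 weeks".

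**The concern.** A secondary outcome should be something a participant can still have or not have after entry. In BUMP 1 the composite works, because CH is excluded and hypertension is what the trial is waiting for. Carried unchanged into BUMP 2, it overlaps with the entry criterion. The analysis then reports a condition that brought the GH women into the trial, and it hides the component that matters, namely who goes on to pre-eclampsia. Since the article names progression to pre-eclampsia as a focus of care once raised blood pressure is found, losing that comparison in the GH stratum is a real loss.

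The subgroup cut has a related problem. A 20-week boundary suits recruitment at 16 to 24 weeks but sits at the very edge of the window in which GH women are recruited directly.

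**Working it through.** **The plan's own BUMP 2 figure.** The inputs from the sample size section are a 5 mm Hg difference, SD 16 mm Hg and 15% attrition. Two-sided 5% and 90% power are stated for BUMP 1 and assumed here for BUMP 2. The t-test calculation gives 217 per group, and 217 / 0.85 = 255.3, which rounds up to the stated 256. The figure reproduces and is not in dispute.

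**Composite, GH stratum.**
- Entry criterion (Box 3): gestational hypertension.
- Outcome (Box 1): pre-eclampsia or gestational hypertension.
- The criterion satisfies the outcome, so the risk is 1 in each arm. Risk ratio = 1/1 = 1, risk difference = 0, and the binomial variance p(1 − p) = 1 × 0 = 0. The log binomial model has nothing to estimate.
- GH women arriving from BUMP 1 qualify because they became hypertensive, so the same holds for them.

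**Composite, CH stratum.** By the Box 3 definition the hypertension was present at booking or before 20 weeks, or was already being treated. New gestational hypertension is therefore not available as an event, and the composite equals pre-eclampsia. It remains estimable.

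**If the strata were pooled for this outcome.** Let g be the GH share, and let the CH risks be 25% in one arm and 15% in the other. These are illustrative assumptions; the article gives no such rates. The pooled risk is g + (1 − g) × CH risk. The CH-only risk ratio is 0.15 / 0.25 = 0.60.

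| GH share g | Risk, arm A | Risk, arm B | Pooled risk ratio |
|---|---|---|---|
| 25% | 0.25 + 0.75 × 0.25 = 0.4375 | 0.25 + 0.75 × 0.15 = 0.3625 | 0.83 |
| 50% | 0.50 + 0.50 × 0.25 = 0.625 | 0.50 + 0.50 × 0.15 = 0.575 | 0.92 |
| 75% | 0.75 + 0.25 × 0.25 = 0.8125 | 0.75 + 0.25 × 0.15 = 0.7875 | 0.97 |

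**Subgroup cut, GH.**
- Direct GH recruits enter from 20+0 to 37+0. Only 20+0 itself is at or below 20 weeks. If completed weeks are meant, 20+0 to 20+6 counts.
- For GH women who come from BUMP 1, the article does not say which date is baseline. If it is the BUMP 1 randomisation, the part of the window from 16+0 to 20+0 falls in the lower group. That group is then made up almost wholly of women from BUMP 1, so early gestation and trial of origin cannot be told apart.
- If baseline is instead the move into BUMP 2, the lower GH group is close to empty from both sources.

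**The case against.** The strongest reply is that Box 1 is a condensed list for two trials, and that how each line is put into practice in each trial is normal analysis-plan content; the article says detailed plans will follow. That would answer a missing detail. It does not answer a statement: the footnote expressly assigns the item to both trials, and the result is degenerate in one of the two analysed strata. Reading the line as two separate outcomes helps only in part, since the gestational hypertension half is still fixed by entry.

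Three stronger readings are tempting, and the documents do not support them.

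- *BUMP 2 loses pre-eclampsia altogether.* It does not. The outcome still works in CH.
- *The lower gestational-age subgroup is empty in GH, or simply separates CH from GH.* This is not established. Women from BUMP 1 were randomised at 16+0 to 24+0 weeks and may carry that baseline. CH women may enter at any gestation up to 37+0. No distribution of entry gestation is given. Nor does the article promise a test of whether late entry limits benefit; late onset is listed only as a limitation.
- *The area under the blood pressure curve mainly measures length of follow-up.* The article says "BP load and area under the curve will be analysed as continuous outcomes by means of a linear regression model" and names BUMP 1 origin as the covariate. A raw area would grow with each day observed, but nothing says that it is raw. Dividing by time is a definition that an analysis plan commonly supplies, so this is not an error in the article.

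**Conclusion.** The main point holds for the GH stratum of BUMP 2. As worded, the composite is met by all women in both arms, the risk ratio is fixed at 1, and this outcome gives no pre-eclampsia estimate there. This follows from the entry criterion and the outcome wording alone and needs no numerical assumption. In CH the outcome is usable. The dilution figures of 0.83 to 0.97 apply only if the strata are pooled, and they rest on the assumed CH risks and GH shares.

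The subgroup point is secondary and narrower. The cut is uninformative for directly recruited GH women. For the whole GH analysis it is either near-empty or confounded with origin, depending on a baseline date that the article leaves open.

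Both points concern secondary or subgroup analyses. The primary outcome and the 256 per group stand. The change should be made before the final analysis.

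**What to change.** 1. In Box 1, keep the composite for BUMP 1 only. For BUMP 2, replace it with pre-eclampsia newly diagnosed after BUMP 2 entry, reported separately for GH and CH. State the entry date that applies to women coming from BUMP 1, so that newly diagnosed has one meaning.
2. For the GH analysis, replace the 20-week cut with gestation at BUMP 2 entry, either with a cut inside the 20 to 37 week window or as a continuous interaction with arm. Women from BUMP 1 are not randomised again, so their gestation at BUMP 2 entry comes after randomisation. The result should therefore also be shown for directly recruited women alone.

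The cost is a few lines in the analysis plan. Item 1 draws on the notes review already planned for maternal outcomes, provided that it records the date of a pre-eclampsia diagnosis. Item 2 uses gestation at entry, which is collected at baseline for direct recruits and can be dated from the notes review for women from BUMP 1. The sample size does not change.
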